## Quality assurance

### CCTA image acquisition and interpretation

All CCTA scans will be performed with single- or dual source CCTA scanners with a minimum of 64 detector rows. Detector row width will be ≤0.75 mm. At a minimum, single-head power injectors allowing fast injection rates of 4–7 mL/s will be required. Laboratories will follow local CCTA scanning protocols as long as they are consistent with quality standards defined by the Society of Cardiovascular Computed Tomography (SCCT) guidelines [21]. CCTA interpretation has also been detailed elsewhere, and will conform to SCCT guidelines [21].

CCTA images will be transmitted to independent masked readers at the CCTA Core Laboratory, who will use dedicated 3-dimensional workstations to evaluate the CCTA images. The 18-segment SCCT model of the coronary tree will be used for the coronary evaluation [21]. Coronary atherosclerosis will be defined as any tissue >1 mm^2^ within or adjacent to the lumen that can be discriminated from surrounding pericardial tissue, epicardial fat, or lumen; and identified in ≥2 planes. Stenoses will be graded in accordance with the SCCT segmental 5-point scale: 0 %; 1–24 %; 25–49 %, 50–69 %, and 70–100 % [21]. Plaque will be measured on 3days workstations, with reconstructions at the smallest slice thickness (~500 μm). All CCTA scans will be interpreted by a minimum of 2 readers, with 20 % randomly repeated to test for inter- and intra-observer variability. APCs and FFR_CT_ analyses will be performed using the already-acquired CCTA data set. CCTA core lab readers and automated software will perform interpretation of APCs. APCs will be studied by multiplanar reconstructions (MPR) and cross-sections using optimal phases, and by automated software with manual correction, with segments classified by an 18-segment SCCT model [21].

### Atherosclerotic plaque characteristics

Given their association to myocardial ischemia in prior studies, six coronary APCs will be selected and will include 1) low attenuation plaque (LAP); 2) positive remodeling (PR); 3) mixed plaque (MP); 4) plaque burden (PB); 5) minimal luminal area (MLA); and 6) transluminal attenuation gradient (TAG) [12, 16, 17, 22]. To determine the incremental value of APCs beyond conventional CCTA measures of CAD, baseline CAD burden by the CAD index and CAD complexity by the SYNTAX score will also be determined [23].

Briefly, a Hounsfield unit (HU) <30 will signify LAP, as this threshold exhibits the best performance compared to intravascular ultrasound (IVUS) [15]. A remodeling index (RI) >1.10 will be defined as PR and a RI <0.95 will be defined as negative remodeling, with in-between values categorized as intermediate remodeling [13]. Plaque composition will be classified on a 5-level scale: non-calcified (0 % calcified plaque [CP]), mostly non-calcified (1–30 % CP), mixed (30–70 % CP), mostly calcified (70–99 % CP), and calcified (100 % CP). Plaque composition scores will be made by summing the number of segments with each type of plaque composition. Finally, TAG will be defined as the change in HU per mm of artery, and will be calculated from the coefficient of linear regression between luminal attenuation and length from vessel ostium [24]. An automated plaque analysis will also be performed with a validated software (QAngio CT, Medis medical imaging systems, Leiden, the Netherlands).

### FFR_CT_ and virtual stenting

FFR_CT_ will be performed by applying a computational fluid dynamics (CFD) approach to typically-acquired CCTA scans for calculation of coronary artery pressure and flow by HeartFlow, Inc. (Redwood City, CA). More detailed information regarding FFR_CT_ and virtual stenting is provided in the online supplementary material, Additional file 1.

### Myocardial perfusion scintigraphy

MPS will be performed by a variety of methods, including PET, SPECT, or CMR. Standard acquisition and analysis protocols will be agreed on for each technique covering patient preparation, cardiovascular stress, administration of radiopharmaceutical or contrast medium, image acquisition and quality control, image processing and interpretation. These procedures will be based on available international guidelines [25, 26].

As such, all MPS studies in this investigation will employ PET when possible. Briefly, dynamic MPS will be performed at rest and during vasodilator stress by 13 N-ammonia (13-NH3) or rubidium-82 (Rb-82) PET using a high-resolution PET/CT scanner, in accordance with societal guidelines [27]. Data will be reconstructed with attenuation correction, based on a validated model from our lab to quantify radionuclide signal attenuation and peak absolute MBF as well as MBF reserve in the territory of the LAD, LCx, and RCA. Time-activity curves will be constructed beginning with initiation of 13-N-NH3 or Rb-82 infusion, using spillover correction [28, 29]. Radionuclide signal in each territory from stress and rest will be compared for calculation of regional (per-vessel) total perfusion defect (rTPD, amount of hypoperfused myocardium as % of total myocardium). Stress-induced perfusion in each territory will be defined as [stress rTPD – rest rTPD], or “reversible” rTPD (REVrTPD), which will be examined continuously for regional myocardial ischemia [30]. In cases when PET cannot be performed, MPS by SPECT will be done and will evaluate perfusion as described above.

For MPS, perfusion in each of the 17 segments will be classified as normal, mild reduction, moderate reduction, severe reduction, or absent perfusion, and the segmental scores were summed for the stress and rest images. An inducible perfusion abnormality will be defined as a summed segmental difference score between stress and rest images ≥2, either from a score ≥1 in ≥2 contiguous segments, or ≥2 in ≥1 segment. Scarring will be defined similarly from the summed segmental rest score. For wall motion abnormalities (WMA), segmental myocardial wall motion will be scored at rest and during stress as normal, hypokinetic, akinetic, or dyskinetic. Inducible ischemia will be defined as an increase in segmental wall motion score ≥1 from rest to stress in ≥2 contiguous segments. Scarring will be defined similarly from the resting wall motion score [31]. The angiographic dominance of the vascular territories will be used for designation of territories during MPS as previously described [32, 33]. In patients with left coronary dominance, the inferior and infero-lateral segments will be assigned to the LCx territory, and all 4 apical segments will be assigned to the LAD territory [33]. In the case of RCA dominance, the inferior, infero-lateral, and apical inferior segments will be assigned to the RCA territory, with the remaining 3 apical segments assigned to the LAD territory [33].

### Invasive coronary angiography and fractional flow reserve

Patients will undergo diagnostic ICA in accordance with usual clinical indications and by imaging standards set forth by the American College of Cardiology/Society for Cardiac Angiography and Interventions [34]. Further detailed information about ICA and FFR procedure is outlined in the online supplementary material, Additional file 1.

### Integration of FFR, CCTA and FFR_CT_ measurements

For suitable comparison of CCTA APCs, FFR_CT_, and FFR, accurate alignment of CCTA and ICA must be performed. An integration process will be performed in a masked fashion by a study investigator not responsible for CCTA, FFR_CT_, or MPS evaluation in order to identify the location of a lesion by CCTA that corresponds to the location where the distal pressure sensor of the wire is located at the time of FFR. The latter integration approach will ensure complete masking of the interpretation of CCTA APCs, FFR_CT_, and ICA and FFR results. On this model, the cardiologist will demarcate the location of the FFR wire, and will refer the model to investigators responsible for interpretation of the CCTA APCs and FFR_CT_.

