**Fig. 1 Fig1:**
[figure not shown]
CREDENCE study design. CAD, coronary artery disease; ICA, invasive coronary angiography; CCTA, coronary computed tomography angiography; MPS, myocardial perfusion scintigraphy; FFR, fractional flow reserve; FFR_CT_, fractional flow reserve derived from coronary computed tomography angiography; APCs, atherosclerotic plaque characteristics; PCI, percutaneous coronary intervention

Importantly, for reasons of safety, all FFRs to be performed will be limited to lesions identified at the time of ICA to be ≥40 and <90 % stenosis, or those that should be clinically indicated for evaluation. As lesions <40 % in diameter stenosis severity are almost uniformly non-ischemic and those ≥90 % are typically ischemic, these lesions should be avoided for interrogation with an FFR guidewire for reasons of patient safety, unless deemed medically necessary. In contrast, coronary stenoses between 40 and 90 % demonstrate variable rates of ischemia and may be appropriately interrogated for clinical indications. If FFR interrogation of a coronary lesion between 40 and 90 % is considered as imparting excess risk to a study subject for anatomical or other reasons, it will be avoided. In keeping with prior studies, vessel territories will be comprised of the left anterior descending artery [LAD] (and diagonal branches), the left circumflex artery [LCx] (and obtuse marginal branches), and the right coronary artery [RCA] (and posterolateral branch and posterior descending artery). Patients who undergo percutaneous coronary intervention (PCI) by intracoronary stenting of ≥1 coronary lesions after the ICA and FFR measurements may have repeat measurements of FFR after the completion of stent deployment, as clinically indicated.

The CREDENCE study will be performed in 19 investigative sites in USA, Canada, Netherlands, Japan, China, Latvia, Italy, and South Korea (ClinicalTrials.gov, NCT02173275). Each center may not enroll more than 40 % of the total number of subjects. The shortest time duration between noninvasive and invasive testing will be at the discretion of the local physician. The maximum time permitted between noninvasive and invasive tests will be 60 days.

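### The article claims complete masking, yet the interpreters of CCTA plaque characteristics and FFR_CT are sent a model showing where the FFR wire lay

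*Protocol article*

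**What the plan says.** Three parts of the protocol article bear on this.

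- *Integration of FFR, CCTA and FFR_CT measurements.* CCTA and ICA are aligned "by a study investigator not responsible for CCTA, FFR_CT_, or MPS evaluation". This approach, the article says, "will ensure complete masking of the interpretation of CCTA APCs, FFR_CT_, and ICA and FFR results". The sentence that follows reads: "the cardiologist will demarcate the location of the FFR wire, and will refer the model to investigators responsible for interpretation of the CCTA APCs". It names the FFR_CT interpreters too.
- *CCTA image acquisition and interpretation.* "CCTA images will be transmitted to independent masked readers at the CCTA Core Laboratory". APCs are read there from reconstructions and cross-sections and "by automated software with manual correction, with segments classified by an 18-segment SCCT model".
- *Methods/Design, text after Fig. 1.* FFR is confined to lesions that ICA shows to be at least 40 % and below 90 %, or that are clinically indicated. The reason given is that "lesions <40 % in diameter stenosis severity are almost uniformly non-ischemic", while lesions of 90 % or more are usually ischemic. A lesion within the range may also be left alone if interrogation carries excess risk.

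On the comparator side, the Discussion has the perfusion studies (MPS) read by a blinded core laboratory. The section on myocardial perfusion scintigraphy gives that reading one angiographic item, coronary dominance, used to assign segments to territories.

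**The concern.** A reader who receives a model with a wire mark learns that the operator found a lesion worth interrogating, in which vessel, and at what point along it. That is information from the reference procedure. It goes to the people who interpret one of the two index tests, while the claim of complete masking stands in the preceding sentence.

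Two features make this more than loose wording. APC measurement includes a manual step that knowledge of the site could influence, and APCs feed the integrated CCTA metric. The disclosure is also one-sided: no marked model is described as going to the MPS readers, and the trial hypothesises that CCTA is superior. The section exempts neither cohort, so testing the metric in the validation cohort would not expose a bias that is present in both.

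**Working it through.** No sample-size or power formula applies to a masking claim. The check is a comparison of the text, followed by two pieces of arithmetic that show what can and cannot be said about size.

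**1. Can the statements all be true?** The article says (a) that the integration masks completely, (b) that the interpreters of APCs and FFR_CT receive the wire location, and (c) that CCTA readers are masked. These are compatible only if the reads are final before the model arrives, or if masking means masking to the FFR value alone. The article states neither.

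**2. What does the mark carry?** Under the FFR rule in Methods/Design:

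| Vessel | What the reader can infer |
|---|---|
| Marked | ICA showed a lesion of 40 % to below 90 %, or there was a clinical indication |
| Unmarked | ICA showed below 40 % (rarely ischemic), or 90 % or more (usually ischemic), or a lesion in range that was passed over for risk |

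The mark carries angiographic information. It does not show whether FFR was above or at/below 0.80.

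**3. Which measurements are exposed?** APCs are exposed through reading and manual correction. FFR_CT is a fluid-dynamics computation (section on FFR_CT and virtual stenting). Apart from the read-out point, the article describes no reader judgement in it, so it is less exposed.

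**4. Which vessels count?** Section (A), on APCs, gives 927 vessels from 309 patients: 309 × 3 = 927, as stated. That count takes in every territory, interrogated or not. Sections (A) and (B) also speak of lesions measured by FFR, and the endpoint is accuracy against invasive FFR. The article therefore leaves open whether vessels without FFR enter the comparison.

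**5. A ceiling, under assumed inputs.** Let u be the share of analysed vessels not interrogated, and a the per-vessel accuracy of CCTA in them under full masking. The document gives neither. If the leak made every such vessel correct and changed nothing elsewhere, accuracy would rise by at most u × (1 − a):

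| u | a = 0.95 | a = 0.90 | a = 0.85 |
|---|---|---|---|
| 0 | 0 | 0 | 0 |
| 0.2 | 1 point | 2 points | 3 points |
| 0.4 | 2 points | 4 points | 6 points |
| 0.6 | 3 points | 6 points | 9 points |

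This is an upper limit for the between-vessel part, not an estimate. It is zero when u = 0. It does not cover the within-vessel cue, which tells the reader which plaque will be compared with FFR.

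**6. A prevalence that should not be used as the size.** For FFR_CT, the Discussion cites an earlier study with per-vessel sensitivity 87.9 %, specificity 82.2 % and PPV 73.9 %. Solving 0.739 = 0.879p / (0.879p + 0.178(1 − p)) gives p = 0.1315 / 0.3610 = 0.364. As a check, accuracy = 0.879 × 0.364 + 0.822 × 0.636 = 84.3 %, and NPV = 92.2 %, both as cited. The arithmetic is sound, but the 36 % describes another study's vessels.

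**The case against.** The best defence is that location is not result. FFR_CT varies along a vessel, so comparing it with FFR requires a matched site, and section (B) calls for one. Among interrogated vessels the mark appears on ischemic and non-ischemic lesions alike, so by itself it cannot separate them. No reader makes an ischemia call, because a regression combines the measurements. MPS is scored by territory and has no use for a wire site. All of this stands, and it limits the point: masking to the FFR value can hold, and what fails is completeness.

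A reader might go further and infer that the mark moves the probability of ischemia from near zero to about 36 %. The document does not support this. Unmarked vessels include lesions of 90 % or more, which the same sentence calls usually ischemic, so they are a mixture and not near zero. The 36 % is borrowed from another study. A reader might also conclude that the result is biased in favour of CCTA. Only the CCTA side receives the mark, which makes the concern reasonable, but neither direction nor size is shown.

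It can also be said that read order belongs in a core-laboratory charter and that a condensed article may omit it. That would answer a complaint about silence. Here the article states both the property and the step that conflicts with it.

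Finally, the Discussion puts comprehensive APC evaluation at 8–10 hours per patient, which might make reading before release look costly. However, the core-laboratory section already has segments classified by the 18-segment model, and the article expects automated software to shorten the work.

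**Conclusion.** The point holds as a contradiction between adjacent sentences. As written, the interpreters of APCs and FFR_CT are not completely masked to ICA/FFR information, because they are shown where the operator chose to measure. This follows from the text and needs no assumption beyond the FFR rule in Methods/Design.

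The consequence is a risk of review bias on the CCTA side of the primary comparison, mainly through manually corrected APCs. Its size cannot be derived from the document. The ceiling of 1 to 9 percentage points of per-vessel accuracy rests on assumed values (u = 0.2 to 0.6, a = 0.85 to 0.95) and falls to 0 if only interrogated vessels are analysed; the within-vessel cue would then remain. If reads are in practice final before the model is released, there is no leak into them and only the wording needs repair.

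**What to change.** Amend the integration section to fix the order of work:

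1. The stenosis reads, the 18-segment APC reads and the FFR_CT computation are completed, time-stamped and locked before the wire-location model is released.
2. Someone other than the reader, for example the separate integration investigator already named there, extracts the locked values at the marked site. Retrieving a locked value is not evaluation, so that person's separation from CCTA and FFR_CT reading is kept.
3. Edits made after the lock are excluded from the primary analysis.

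If this order is already followed, the article need only say so. If it cannot be followed, the masking statement should be restricted to the FFR value, with the disclosure of the interrogated site acknowledged.

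The cost is a sentence or two of workflow, a lock flag in the database and a slight delay between read and extraction. No additional readers are needed.

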## Organization and data management

This study will be coordinated by the Dalio Institute of Cardiovascular Imaging Clinical and Data Coordinating Center (DICI CDCC). The DICI CDCC will be responsible for the processing and quality control of the data. The study protocol will be approved at each participating center by the local institutional review board. Completed electronic case report forms (eCRFs) will be entered by trained site personnel, and will be transmitted to a central data repository at the DCC. At regular intervals, all data will be transferred from electronic case report form (REDCAP) to SAS for statistical summarization, data description, and data analysis. Further cross-checking of the data will be performed in SAS.

Site qualification will be issued by the DICI CDCC for each modality before subject enrollment. Before beginning enrollment, eligible sites will be qualified by the imaging Core Laboratories based on site surveys and on successful transfer of one or more complete datasets with sufficient image quality and completeness for each modality. During the study, technical quality assessment of image and test acquisition will be accomplished on all studies by central repository research technicians trained by the CDCC. This ongoing review will ensure the adequate quality and completeness of datasets.

## Discussion

The CREDENCE study aims to integrate the anatomic and physiologic information derived from CCTA for the precise identification of ischemia-causing coronary lesions, and to compare this measure against an integrated metric for MPS. To date, no non-invasive imaging modality has been routinely capable of a “one-stop shop,” wherein anatomic identification of stenoses and physiologic determination of ischemia are derived from a single test, thus resulting in layered testing and increased complexity and cost of clinical care. Specifically, this study will assess the performance of anatomic APCs by CCTA and physiologic FFR_CT_ for diagnosis of vessel-specific ischemia. An integrated APC-FFR_CT_ metric by CCTA will then be directly compared to a perfusion-MBF-ECG-functional capacity metric by MPS for diagnosis of vessel-specific ischemia. As such, we hypothesize that an integrated assessment by CCTA will be superior to an integrated assessment by MPS for the diagnosis of vessel-specific ischemia.

Prior studies have established that MPS is capable of determining the severity and extent of myocardial ischemia with high performance at a per-patient level, and that MPS evaluation is augmented by MBF, ECG, and functional capacity findings [5, 6]. Nevertheless, the “real world” accuracy of MPS is less assertive despite its high reported diagnostic performance [35]. To date, no study has included the totality of information imparted by MPS—including MBF, ECG, and functional capacity—rendering comparisons of CCTA to MPS incomplete and, in general, skewed towards improved CCTA diagnostic performance.

CCTA has demonstrated high performance for diagnosis of obstructive CAD compared to ICA, and predicts adverse prognosis [36]. In the prospective multicenter ACCURACY trial, CCTA demonstrated a sensitivity, specificity, PPV and NPV of 94, 83, 48, and 99 %, respectively, compared with ICA. The results of this ACCURACY trial are in agreement with two subsequent multicenter studies that demonstrated high accuracy of CCTA [10, 11]. On the contrary, even though CCTA can discriminate stenosis with high accuracy, the ability to identify ischemia-causing coronary lesions is suboptimal at present [12]. In a study of 79 patients undergoing CCTA and ICA with FFR, high rates of false positive CCTAs were noted, with an overall specificity for ischemia of 40 % [12]. Similar findings have been observed from pooled analyses comparing CCTA to MPS wherein CCTA stenoses were associated with ischemia less than half of the time [37, 38].

The PROMISE trial demonstrated equivalent outcomes between functional imaging by multiple modalities, including PET, and anatomic evaluation of stenosis severity by CCTA [39]. The CREDENCE trial posits that stenosis evaluation alone discards important anatomic and functional data in routinely performed CCTA, and that a combined assessment may be superior for vessel ischemia. Similarly, the CREDENCE trial posits that perfusion evaluation alone by MPS discards important functional information, and that combined assessment may be superior for vessel ischemia. Prior studies have shown that CCTA enables assessment of several coronary APCs with generally high accuracy beyond luminal diameter stenosis, and similar to invasive studies by intravascular ultrasound, APCs visualized on CCTA have been associated with ischemia-causing culprit lesions [40] [14, 15, 17]. Further still, the accuracy of FFR_CT_ for diagnosing coronary ischemia has been reported in several studies [19, 41, 42]. In the DISCOVER-FLOW (Diagnosis of Ischemia-Causing Stenoses Obtained Via Noninvasive Fractional Flow Reserve) trial, compared with invasive FFR, non-invasive FFR_CT_ demonstrated per-vessel accuracy, sensitivity, specificity, PPV, and NPV for ischemia-causing lesions of 84.3 %, 87.9 %, 82.2 %, 73.9 %, 92.2 %, respectively [19]. Further, in a more recent HeartFlow NXT study, the FFR_CT_ data matched closely with invasively measured FFR [42].

To date, however, clinical reporting of CCTA has been limited to stenosis severity, with relative neglect of APCs and unavailability of FFR_CT_. The aversion to incorporate APC findings may originate from the fact that APC quantification is time-intensive with per-patient evaluation taking 8–10 h for comprehensive APC evaluation. This study will facilitate widespread applicability by assessing co-linearity of APCs to develop the most parsimonious set of APCs that offers the greatest diagnostic value; and validate the diagnostic utility of the APCs in a separate cohort of individuals. We have ensured that APC measures will be accurate by several safeguards. We will use images only from CCTA scanners with 64-rows or more, the threshold for adequate coronary imaging by CCTA. Further, APCs will be interpreted at a state-of-the-art laboratory by ≥2 readers with inter- and intra-observer assessment for a 20 % of CCTAs for assurances of reliability. Similarly, this study will assess FFR_CT_, referenced against both invasive FFR and non-invasive stress test “gold” standards. Furthermore, this study will perform APC and FFR_CT_ evaluation with automated software that will facilitate time-efficient evaluation of both APCs and FFR_CT_.

Similar to CCTA, we will perform a comprehensive assessment of MPS. By a dedicated and blinded core laboratory, we will examine factors beyond regional myocardial perfusion, and will include imaging high-risk features of CAD (including transient ischemic dilatation, and increased lung uptake of radiotracer), as well as high-risk ECG features (such as ST-segment depression, hypotensive response to stress, heart rate recovery, and rate-pressure product). Functional capacity and MBF will also be assessed.

If proven successful and the superiority of a combined anatomic-physiologic approach is shown, this trial will provide the rationale in developing and establishing a novel diagnostic paradigm that not only identifies patients who manifest ischemia, but also specify ischemia-causing coronary lesions that may be more accurate than conventional stress imaging. If the strategies are equivalent, there will still be information gain in determining the most efficient means to determine lesion-specific ischemia by CCTA and MPS. The results of this approach may reduce the number of missed diagnoses and help to optimally predict ischemia-causing lesions, considering the fact that millions of patients are tested for CAD each year in the US alone. Further, this novel diagnostic paradigm may help promote avoidance of unnecessary invasive procedures and procedure-related complications in the future, and allow for improved clinical decision-making to identify patients who are versus who are not eligible for coronary revascularization. Finally, the proposed trial will potentially reduce downstream care related to these invasive procedures as well as the cost burden, and directly impacts annual healthcare savings.

